## Abstract

Climate change is intensifying the frequency and severity of heatwaves, posing growing risks for workers. Home care workers face heightened heat risks due to physically demanding tasks, rising patient needs, frequent travel, and limited access to cooling environments. This study aims to causally evaluate the effectiveness of an app-based intervention (REHEAT strategy) in reducing adverse effects of heatwaves among Swiss home care workers. This multicenter, unblinded, randomized controlled trial (RCT) will involve 350 home care workers from the regions of Northern and Southern Switzerland. Participants will be randomized (1:1) into intervention and control groups, stratified by sex, age group, and geographical location. The intervention group will use the REHEAT app from June to September 2025, while the control group will gain access only after summer 2025. Both groups will be monitored over the summer using a wrist-worn wearable device (smartwatch), online questionnaires, diaries and cognitive tests. The impact of the REHEAT intervention will be evaluated using an Intention-To-Treat (ITT) approach to provide reliable real-world effect estimates, supplemented by Local Average Treatment Effects (LATE) analyses to assess impact based on participant exposure and compliance levels. Primary outcomes include strain accumulation, cognitive performance, emotional distress, sleep, night recovery, and mental and physical health. Outcomes will be analyzed longitudinally with mixed-effects models, while LATE will be estimated using app usage as an instrumental variable in generalized linear mixed models. At the time of submission, recruitment had been successfully completed, with a total of 350 participants enrolled in accordance with the study protocol. The intervention and data collection phases are ongoing, and no outcome data have yet been accessed or analyzed. The findings will inform the development of occupational health interventions in response to heat-related stressors and support climate change adaptation policies for health sector workers.

● Climate change intensifies heatwaves, posing growing risks for exposed workers.● An RCT protocol assesses an app-based heat adaptation strategy for home care workers.● A co-designed app provides tailored tips, alerts, and resources for heat protection.● Tested in a Swiss multi-center RCT with physiological, self-report, and meteo data.● The strategy and protocol are a scalable to other workforces and contexts.

## Introduction

### Background

During the past decades, human-induced climate change has lead to an increase in the frequency, length and intensity of heatwaves.^1
[Bibr bibr2-00469580251405766]-3^ Heatwaves represent a significant threat to human health,^4
[Bibr bibr5-00469580251405766]-6^ and large body of research shows that children, pregnant women or elderly people are especially at risk of heat exposure.^7
[Bibr bibr8-00469580251405766]-9^

More recent evidence indicates that the working population also faces an elevated risk of heat exposure.^5,10
[Bibr bibr11-00469580251405766][Bibr bibr12-00469580251405766]-13^ This is especially true for workers employed outdoors, in environments with high temperatures, or engaged in physically and mentally strenuous tasks.^14,15^ Elevated risk arises both from constraints in the context of work, such as time pressure, and from the intensity of the occupational activity.^
16
^ Research has shown that adverse effects of heat while working can occur already at temperatures lower than those for which public warnings are issued.^17,18^

Previous research on the effect of heat on workers’ health has mainly focused on the economic sectors of construction and agriculture.^
14
^ Less is known about female dominated economic sectors such as health care. First studies indicate that among health care professionals, home care workers are particularly at risk.^
19
^ This is due to their work tasks, which require outdoor commuting between their clients’ residences, working in private—often not air-conditioned—homes, and the performance of physically intense activities, such as lifting people. In addition, they frequently face tight schedules. These working conditions do not only lead to physical strain accumulation but also may affect their cognitive performance, emotional distress, sleep, night recovery, and mental and physical health.^14,20
[Bibr bibr21-00469580251405766]-22^

In addition to these direct effects of heat on health, there may also be indirect effects. Heat waves can lead to an increase in service demand.^
23
^ In fact, there may be increased requests for additional assistance from elderly, disabled, or chronically ill people, who are particularly vulnerable to heat.^24,25^ Moreover, home care workers often implement preventive strategies to protect their clients from the heat, such as opening windows early in the morning or motivating clients to drink enough water. An increased service demand likely results in an additional strain accumulation among home care workers, who may already experience effects of the heat on their health.^
26
^

Given the evidence about health risks of heat waves, there is an urgent need to find effective strategies to attenuate these risks among home care workers.^
27
^ While general heat adaptation strategies are widely known (eg, hydration, restriction of strenuous activities, seeking of shade and cool places), implementing them in the specific context of home care is more challenging.^
15
^ Previous research indicates, for instance, that sufficient hydration is often not achieved due to time pressure and lack of access to sanitary facilities.^
28
^

The development and implementation of heat adaptation strategies among home care workers is not only in the interest of workers but also of their employers and society as a whole.^15,17^ Improving the resilience of the health care system during heat waves substantially contributes to the general societal resilience in the context of rapidly advancing climate change.^29,30^

### Home Care in Switzerland

In Switzerland, home care organizations provide professional home care for people of all ages who need support due to illness, disability, aging, or recovery after hospitalization.^
31
^ Both publicly mandated non-profit organizations and private providers deliver these services.^
32
^

Home care is individually tailored and includes medical and nursing services such as care assessment, medication management, pain and wound treatment, and monitoring of vital signs. Specialized services cover areas like oncology, palliative, psychiatric, and pediatric care.^
31
^ Basic care focuses on personal hygiene, mobility, and eating assistance, while household support includes shopping, cooking, cleaning, and laundry. Depending on the region, additional offers such as meal delivery, medical transport, and equipment rental may be available. In 2024, 2971 organizations with around 64 000 employees provided home care services nationwide.

Funding follows a dual model.^32,33^ Compulsory health insurance covers nursing care under standardized tariffs, while patients contribute through deductibles and daily co-payments. The remaining costs are shared by cantons and municipalities, with some expenses potentially passed on to clients. Household assistance is excluded from basic insurance and thus is financed privately or through supplementary insurance.

### Rationale of the REHEAT Study

Despite the recognition of heat-related health risks in the home care sector, home care workers have received limited attention in research on human adaptation to climate change. Existing research programs such as HEATSHIELD (Europe)^
34
^ or Too Hot To Work (Australia)^
35
^ mostly focused on male-dominated sectors such as construction, neglecting the unique needs of female workers, who make up the majority of the home care workforce. Consequently, more research is needed to understand, first, how heat waves specifically affect home care workers’ health, and second, to identify heat adaptation strategies that can be effectively implemented in the home care setting.^15,36,37^

The project “Home caRE workers’ Health risks of Exposure to heAT waves. Solutions for human adaptation to climate change in the context of working life extension (REHEAT),” based in Switzerland, seeks to address these gaps. In the REHEAT project, we first assess the effect of heat waves on home care workers’ health, focusing on outcomes such as strain accumulation or mental health. Second, we evaluate the effectiveness of a heat adaptation strategy (REHEAT strategy) developed in collaboration with home care workers and experts from 2 Swiss regions. The REHEAT strategy is grounded in a participatory “living lab approach,” aimed at tailoring recommendations and resources to the lived realities of workers.^38
[Bibr bibr39-00469580251405766]-40^ It will be delivered through a smartphone-based app (REHEAT app), offering guidance on hydration, nutrition, clothing and rest, and providing home care workers with heat protection alerts and local resource maps.

According to the Federal Act on Research involving Human Beings (Human Research Act, HRA),^
41
^ REHEAT is classified as an “other clinical study,” as it involves providing home care workers with training materials and behavioral incentives to increase their awareness of heat protection and encourage the adoption or consolidation of health-protective behaviors. REHEAT falls under risk category A, as it entails only minimal risks and burdens for participants. Specifically, data are collected solely via surveys and wrist-worn wearable devices (smartwatches), and no invasive or potentially harmful interventions are implemented at any point during the study.

### Objectives

This protocol (Version 1, dated 3 September 2025) outlines a randomized controlled trial (RCT) designed to rigorously assess the REHEAT strategy’s effectiveness in preventing the adverse effects of heatwaves among home care workers in 2 regions of Switzerland. The protocol is developed in accordance with the SPIRIT 2025 statement,^
42
^ and the corresponding checklist is included in the Supplemental Material.

The primary objectives of the RCT are:

To causally assess the effectiveness of the app-based REHEAT strategy in reducing negative heat-related health and well-being impacts among home care workers.To examine whether effects vary by worker characteristics such as age, sex, and geographical location.To evaluate participants’ compliance and satisfaction toward the app-based strategy.

### Hypotheses

In light of the above-mentioned objectives, the following hypotheses are proposed:

Overall effect: Among home care workers in Switzerland, the REHEAT strategy will reduce the adverse effects of heat exposure, including: strain accumulation, cognitive impairments, emotional distress, sleep disturbances, limited night recovery, and declines in mental and physical health.Age-related heterogeneity: The REHEAT strategy will be more effective for older workers aged 50 and above, with stronger reductions in heat-related adverse effects expected than for younger workers.Sex-related heterogeneity: The REHEAT strategy will be more effective for female workers, who are expected to experience greater benefits compared to their male counterparts.Geographical consistency: Due to the inclusion of practitioners from both regions in the development of the REHEAT strategy, it will be equally effective across geographical areas, with similar impacts observed in both Southern, Italian-speaking, and North-Eastern, German-speaking Switzerland.User engagement: Due to the participatory living lab approach applied for the development of the REHEAT strategy, participants are expected to show high levels of compliance and satisfaction with the REHEAT strategy.

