**Figure 3. fig3-00469580251405766:**
[figure not shown]
REHEAT data collection System and metrics.

A growing body of research highlights the advantages of integrating traditional survey methods with mobile and wearable technologies to gain more nuanced insights into individuals’ daily experiences and behaviors.^
45
^ These technologies support the continuous collection of high-resolution physiological and contextual data while minimizing the user burden, thus reducing recall bias and social desirability effects commonly associated with self-reports.^
46
^ The combination of “passive” sensing and traditional surveys allows for the joint analysis of objective indicators and subjective perceptions, including emotional states, routines, and situational appraisals.

The overall impact of the REHEAT strategy and the heterogeneity of its effects between groups is assessed through key primary outcomes, including strain accumulation, cognitive performance, emotional distress, sleep and night recovery, and mental and physical health. Secondary outcomes include objective and self-reported measures of intervention compliance, manipulation checks, and user experience and satisfaction. The complete list of study outcomes, along with detailed descriptions of their sources, data collection methods, and characteristics, is provided in Table 1.

**Table 1. table1-00469580251405766:** Summary of REHEAT Primary and Secondary Outcomes.

Outcome	Domain	Source	Time frame	Measurement description
*Primary outcomes*				
Strain accumulation	Physiological & psychological load	Garmin smartwatch; app-based questionnaires	Daily, with a focus on baseline vs heatwaves occurrence	Objective physiological heart rate metrics (HRV); self-reported stress (VAS)^ 47 ^ and daily activities
Cognitive performance	Cognitive function	App-based cognitive tests	Daily, with a focus on baseline vs heatwaves occurrence	Task-based cognitive performance via the short tests serial-seven^ 48 ^ and delayed recall^ 49 ^
Emotional distress	Psychological well-being	App-based questionnaires	Daily, with a focus on baseline vs heatwaves occurrence	Positive and Negative Affect (I-PANAS-SF)^ 50 ^

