^ Potential time-invariant characteristics of the respondents (eg, years of experience in home care, chronic conditions), and time-varying confounding due to intermediate variables (eg, workload changes, night shifts) are also addressed in sensitivity analyses.

Effect Heterogeneity: interaction terms are included in multilevel models to explore differences in outcomes by sex, age, geographical region, and time-related factors. Separate models assess moderation effects by these variables in both ITT and LATE frameworks. Random intercept multilevel regression techniques are used to model hierarchical longitudinal data that violate the independence assumption (ie, repeatedly measured continuous outcomes). The heterogeneity of heat episode effects are estimated by multiple-interaction models in which interaction terms between the heat episode, the participant’s area of work, age, and sex are estimated. To capture temporal heterogeneity, additional interaction terms assess whether the REHEAT strategy differentially mitigates heat effects over the course of the summer. Treatment-by-time interactions, such as calendar week, cumulative heat exposure, or time since onboarding, are used to examine whether intervention effects vary due to seasonal acclimatization or repeated exposure.^
59
^ Flexible calendar-week splines and random slopes for time allow for individual adaptation trajectories and evolving heat vulnerability. These analyses determine whether the REHEAT strategy effectively addresses the diverse and changing needs of home care workers operating in different areas of Switzerland, who are exposed to different climatic, organizational and contextual conditions, while also estimating average conditional treatment effects across demographic and temporal dimensions.

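### Age and sex effect variation is a primary objective with directional hypotheses, but it is tested by unprioritised interactions over all primary outcomes and two frameworks in a trial sized for one overall comparison

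*Protocol article*

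**What the plan says.** Under Objectives, the list headed "The primary objectives of the RCT are" includes this item: "To examine whether effects vary by worker characteristics such as age, sex, and geographical location". Under Hypotheses, two of the stated expectations are directional: "The REHEAT strategy will be more effective for older workers aged 50 and above", and "The REHEAT strategy will be more effective for female workers, who are expected to experience greater benefits compared to their male counterparts". Trial Design adds that the design supports robust estimation of the average effect and also of its heterogeneity across subgroups.

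Under Outcomes, "the heterogeneity of its effects between groups is assessed through key primary outcomes". Table 1 has six primary rows, most of them with several measures. The Effect Heterogeneity part of the Statistical Analysis Plan section says that "interaction terms are included in multilevel models to explore differences in outcomes by sex, age, geographical region, and time-related factors" and that "Separate models assess moderation effects by these variables in both ITT and LATE frameworks". It adds models with several interactions at once and treatment-by-time terms, and then states: "These analyses determine whether the REHEAT strategy effectively addresses the diverse and changing needs of home care workers".

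Sample Size Calculation sizes a two-arm comparison of one continuous outcome at two-sided 5% and 80% power.

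**The concern.** The same analyses are given two standings. Objectives and Hypotheses read as claims to be confirmed, and Trial Design calls the heterogeneity estimates robust. The analysis section uses the language of exploration and then says that the analyses settle the matter. Neither the hypotheses nor the analysis section ties the age or sex hypothesis to a particular outcome or framework. An author who finds one significant arm-by-age or arm-by-sex term, on any primary outcome and under either framework, could present it in good faith as support for a primary-objective hypothesis.

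The Conclusion says the findings will feed into occupational health guidelines and policies, so advice to target older or female workers could rest on a chance finding. The problem is separate from multiplicity in the overall-effect tests, because correcting those would leave the subgroup claims unprotected.

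**Working it through.** **Inputs from the article.** Six primary rows (Table 1); two directional hypotheses, age and sex; two frameworks, ITT and LATE; two-sided 5% and 80% power; 1:1 allocation; a total of 330 to 370 with about 10% added as a safety margin; 350 enrolled.

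**Assumptions.** The outcome correlations, the ITT-LATE correlation and the subgroup shares are not given. Age and sex tests are treated as independent of each other, and each outcome is counted once.

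**The plan's own figure.** The sample size cannot be reproduced, because neither σ nor ∆ is reported as a number. Only the margin can be checked: 330 × 1.1 = 363 and 330 / 0.9 = 367, both close to 370. Taking 330 as the unpadded total (165 per arm), the implied standardised effect is (1.96 + 0.84) × √(2/165) = 0.308 SD.

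**False directional findings with no true heterogeneity.** One two-sided 5% test gives a false finding in the hypothesised direction with probability 2.5%. Two such tests give 1 − 0.975² = 4.9%.

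- *Independent outcomes, ITT only.* Per hypothesis: 1 − 0.975⁶ = 14.1%. Age or sex: 1 − 0.975¹² = 26.2%.
- *Correlated outcomes, ITT only.* Simulation of six equicorrelated z-statistics per moderator, counting any z > 1.96:

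| Correlation | One hypothesis | Age or sex |
|---|---|---|
| 0.2 | 13% | 24% |
| 0.5 | 10% | 20% |
| 0.8 | 7% | 13% |

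- *ITT plus LATE.* With outcome correlation 0.3 to 0.7 and ITT-LATE correlation 0.7 to 0.9, age or sex gives 21% to 35%. If all 24 tests were independent, the figure would be 1 − 0.975²⁴ = 45.5%, an upper bound because ITT and LATE share the same data.

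**Power for an interaction.** If a share p of participants is in one subgroup, each person counted as one measurement, the standard error of the arm-by-subgroup contrast in SD units is (2/√N) / √(p(1 − p)). This is at least twice the main-effect standard error of 2/√350 = 0.107. Power is Φ(0.308/SE − 1.96).

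| Share p (assumed) | SE | Power for 0.308 SD |
|---|---|---|
| 0.50 | 0.214 | 30% |
| 0.40 | 0.218 | 29% |
| 0.30 | 0.233 | 26% |
| 0.15 | 0.299 | 18% |
| 0.10 | 0.356 | 14% |

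An even split is the best case, so no share takes power above about 30%. With 10% men, an observed interaction must exceed 1.96 × 0.356 = 0.70 SD to be significant, more than twice the implied overall effect.

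**The case against.** The strongest reply is that the article does not really treat these analyses as confirmatory. The objective says 'examine' and the analysis section says 'explore', which agree. The primary-objectives list also includes compliance and satisfaction, which Table 1 classes as secondary outcomes, so that list may simply name the study aims. No sentence says that one significant interaction confirms a hypothesis. A separate analysis plan may contain multiplicity rules, and their absence from an article is not a fault. The subgroup factors are also few, named in advance with a direction, cut at a fixed age of 50 and used as randomisation strata.

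Much of this stands. Missing multiplicity rules alone would not carry the point, and the choice of subgroup factors is good practice. However, pre-specified factors do not control error over six outcomes and two frameworks. Nor can an analysis plan held elsewhere reconcile directional hypotheses, a claim of robust heterogeneity estimation and an unprioritised exploratory analysis, all of which stand in the current text.

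The power figures are also open to challenge: the effect is back-solved, repeated measures are ignored and the share of men is assumed, since the article says only that women are the majority of the workforce. Repeated measures should help the overall and interaction contrasts about equally, so the relative loss of precision roughly persists.

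A reader might infer that a false claim of greater benefit in older or female workers is likely. The figures do not support that. Over the six outcomes the directional risk is 13-24% in ITT and about 21-35% with LATE. Counting interactions in either direction gives 37% (six outcomes, correlation 0.5, ITT only), but some of those would contradict the hypotheses. Treatment-by-time terms cannot produce a false age or sex claim and do not belong in this count.

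**Conclusion.** The point holds as a mismatch between the status given to the subgroup hypotheses and the way they are tested. On the ITT analysis alone, the chance of falsely supporting the age or sex hypothesis is about 20% (13-24%), roughly four times the 5% of two single tests. Per hypothesis it is about 10% (7-13%) against 2.5%. Power is at most about 30% for an interaction as large as the implied overall effect, and about 14% for sex if 10% of participants are men. A significant interaction would therefore be weak evidence and probably exaggerated in size.

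The error rates rest on one test per primary row and the assumed correlations. The power figures rest on 330 as the unpadded total, one measurement per person and the assumed shares; the ceiling of about 30% does not depend on the share. The change should be made, since it affects what the trial may conclude.

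**What to change.** In Objectives, Hypotheses, Trial Design and the Effect Heterogeneity text, label the age, sex, geographical and time heterogeneity analyses exploratory. Report interaction estimates with 95% confidence intervals, and state that no confirmatory subgroup claim rests on them. In the Effect Heterogeneity text, change 'determine whether' to 'explore whether'. In Trial Design, no longer apply 'robust' to heterogeneity.

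If the sponsor wants the age and sex hypotheses to be confirmatory, one option is to test each once, as the arm-by-age and arm-by-sex term in the ITT model on one named outcome, with Holm's procedure across the two. All other outcomes and all LATE moderation would remain exploratory.

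The cost is wording only, with no new data or participants. The article reports that no outcome data had been accessed at submission; the change should be dated against that point. The downside is that a lone significant interaction can no longer be presented as confirming a hypothesis.
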